#### Modification and risk–benefit assessment

Possible benefits for the participants are improvements in activities or participation despite existing functional limitations due to joint contractures plus a reduction in the risk of further joint contractures. No modification of PECAN is planned, and no side effects, risks or complications are expected due to participation in the intervention. However, possible complications will be identified through the continuous close peer mentoring and reacted to promptly. In addition, the facilitators will be encouraged to talk directly to the relevant researchers, should problems arise. In the pilot study, there were no relevant differences between the intervention and control group regarding potential adverse events, such as the frequency of falls and fall-related fractures, nor was there any relevant increase in comparison to the baseline.

#### Control group

The nursing home residents in the control group will receive optimised standard care based on the usual care plus a brief in-house presentation of 45 min for nursing home staff, mainly nurses and additional care helpers. The session will cover information on the study, on the development of joint contractures, and on their relevance for daily life and the social participation of the affected individuals. It will also include a basic overview of current evidence, excluding intervention-related details.

To avoid contamination between the intervention and the control groups, the participating nursing homes will be obliged to refrain from actively disseminating intervention components to any other institutions, especially to other nursing homes in the control group. After the intervention period, nursing staff from the control group are given the opportunity to attend the workshop for facilitators and to receive the educational material and handbook free of charge.

### Outcome measures

Data for outcomes and other variables will be collected at three measurement points: at baseline before randomisation (t_0_), after 6 months (t_1_), and after 12 months (t_2_). Table 1 provides an overview of the different variables on an individual level, which includes the ratings of the nursing home residents. We will assess the cognitive status of the residents at each time point to decide if the outcome measurements will require a proxy rating, which the nursing staff will perform.

**Table 1 Tab1:** Instruments and measures at resident level

Instrument	Outcome	Measurement point		
		t_0_	t_1_	t_2_
Primary outcomes				
PaArticular Scales, subscale participation [17]	Participation	X	X	X
PaArticular Scales, subscale activities [17]	Activities	X	X	X
Secondary outcomes				
EQ-5D-5L [34, 35]	Health-related quality of life	X	X	X
Additional data sources				
Medical records	Clinical data	X	X	X
DSS [36]	Cognitive impairment	X	X	X
CMAI [37, 38]	Behavioural symptoms	X	X	X
Clinical records	Falls and fall-related consequences	X	X	X
Clinical records	Physical restraints	X	X	X

*CMAI* Cohen–Mansfield Agitation Inventory, *DSS* Dementia Screening Scale, *EQ-5D-5L* EuroQol Five-Dimension Five-Level Instrument, *t*_*0*_ baseline before randomisation, *t*_*1*_ 6 months post-randomisation, *t*_*2*_ 12 months post-randomisation

#### Primary outcome

The initial objective of the project was to improve participation in nursing home residents with joint contractures. However, the results of the pilot study suggested that an improvement in participation is difficult to realise, especially within a population undergoing cognitive decline. Since activities and participation are related but independent constructs with no ranking, we decided that an improvement in any of the scales could be viewed as success. Therefore, the selected primary outcomes assess the nursing home residents’ participation and activities, which are measured with the two subscales of the ICF-based PaArticular Scales [17], a patient-centred self-reported measure. The PaArticular Scales were developed in a previous project using item response theory (Rasch analysis) based on a standard set of questions for joint contractures [15]. The instrument has two independent subscales. The participation subscale measures the impact of joint contractures on the participation of a person, i.e. the social perspective of functioning involving interactions with other people. It has 11 items on topics such as community life, sports, crafts and socialising. The activities subscale measures the impact on aspects of life related to mobility and self-care. It has 24 items on topics such as changing and maintaining body position, walking and moving, carrying, moving and handling objects, dressing and eating.

The scales were developed and validated in a sample of nursing home residents and patients in geriatric rehabilitation who were affected by joint contractures. The items were selected in a comprehensive standardised procedure in line with the suggestions for developing ICF core sets [39, 40]. The Rasch modelling approach to constructing scales based on items from the ICF has been shown to be valid in other studies [41, 42]. Before any analyses on the primary outcome are carried out, the psychometric properties of the PaArticular Scales will be re-evaluated in a Rasch-analysis of the data from the pilot study.

For each subscale, the nursing home resident or, if not possible, a proxy (nurse), assesses their existing difficulties for the different items on a scale ranging from 0 for “no problem”, 1 for “mild to moderate problem” and 2 for “severe problem” to 3 for “complete problem”. Additionally, an item is assigned “C” if the difficulty can be assigned without doubt to a cause other than the contracture. For both the participation subscale and the activity subscale, the scores are summed to give an initial ordinal raw score. This is transformed into an interval scaled score, ranging from 0 to 100, to allow comparisons at the interval level.

A mean decrease of ten points on the participation or activity subscale of the PaArticular Scales at t_2_ is considered as a clinically meaningful difference in favour of the PECAN intervention. This would represent a change from “complete problem” to “mild/moderate/severe problem” or from “mild/moderate/severe problem” to “no problem” in one of the patient-relevant items. The ten-point difference is also in line with the suggested distribution-based methods for defining a minimally important difference as at least 1/2 of the standard deviation [43], because the standard deviation in the baseline data from our pilot study is about 14, which is below 20.

In a recent review of the test–retest reliability of patient-centred self-reported measures for older people, the methodological quality of the PaArticular Scales was assessed as “fair” [44].

#### Secondary outcome

The secondary outcome is the nursing home residents’ quality of life. We will assess health-related quality of life at t_0_, t_1_ and t_2_, using the German version of the internationally established generic instrument the European Quality of Life Five-Dimension Five-Level Scale (EQ-5D-5L) [34, 35]. The residents can rate their health status using the following five dimensions: mobility, self-care, usual activities, pain/discomfort and anxiety/depression. Each dimension has five levels: no problems, slight problems, moderate problems, severe problems and extreme problems. Furthermore, a vertical visual analogue scale (EQ-VAS score) records a resident’s self-rated health from best to worst imaginable (range 0–100). In the corresponding proxy version, the nursing staff will be asked to rate how they think the residents would rate their own health-related quality of life, if they were able to communicate it.

#### Additional measures

We will collect further data for descriptive purposes (see Table 1). On an individual level, we will collect clinical data such as length of stay at baseline. In addition, we will collect grade of care, urinary and faecal incontinence, affected joints, provision of adaptive technologies, medical aids, physical therapy and occupational therapy at each time point. Additional characteristics will be collected from nurses’ assessments of the residents’ cognitive status and behavioural symptoms that are related to dementia.

A nurse will rate the cognitive status of each resident during the last month of the intervention using the Dementia Screening Scale (DSS) [36] to assess whether a proxy rating is required. The DSS contains the dimensions memory and orientation, giving a total of seven items each with a three-point scale (never, occasionally or always). The tallied responses result in an overall score with a range from 0 to 14, higher values indicating a greater degree of cognitive impairment. A proxy rating is performed at a cut-off point of 3.

The residents’ behavioural symptoms will be determined using a modified German version [45] of the Cohen–Mansfield Agitation Inventory (CMAI) [37, 38], as used in previous studies [46, 47]. The inventory consists of five symptom complexes: restlessness, verbal agitation, handling things inappropriately, negative attitude and aggression. Each complex is rated on a four-point Likert scale (never, once or twice, repeatedly, permanently) that assesses symptoms within the preceding four weeks.

On a cluster level, we will record the ownership of the nursing home (public, non-profit-organisation or private), its location and surroundings, the number of residents, the number and size of wards, the number of residents with joint contractures, staff mix and ratio, and the use of strategies for dealing with joint contractures or participation restrictions by interviewing the director of the nursing homes or head nurse at baseline.

To document adverse events that are potentially associated with the PECAN intervention, we will collect data on an individual level concerning the incidence of falls, fall-related consequences as well as the number and types of physical restraints used.

#### Data collection and management

All assessments will be performed on a paper-and-pencil basis by blinded members of the research team, who will be thoroughly trained in the data collection procedure.

Only pseudonymised data will be collected at the study centres in Halle (Saale) and Rosenheim, i.e. no personal data about the participants will be recorded or saved. The participating nursing homes will be allocated a pseudonymised number. To compare the outcomes from the measurement points, each participant will be assigned a code from a list, which will be stored separately and can be accessed only by the researchers at the study centres. The list will never be merged with the pseudonymised data and will be destroyed after the final validation of the analysis data set.

After each measurement point, the paper-based pseudonymised data at resident level from the study centres in Halle (Saale) and Rosenheim will be transferred to the biostatisticians’ institution, where the data entry and analysis will be performed by the data managers and biostatisticians. A copy of the questionnaires will remain safely stored at the respective study centres.

All answer to the questionnaires will be entered into a database and validated through double entry. The first data entry will take place at the latest 1 month after the different time points. Additionally, the data will be checked for inconsistency and completeness and its quality will be reported to the study centres.

The pseudonymised data will be stored on a secure computer. These data will be handled in accordance with the data protection declaration of the biometric institution. The server and all connected data arrays are in a limited access server room that is protected by a key card system and an alarm. The data will be encrypted and password-protected when being transferred between secure servers. Any hard-copy printouts, USB data versions or other removable media that are used to transfer protected health information will be destroyed after the transmission is complete.

Given the nature of the intervention, we do not expect either any serious safety concerns or an early termination of the study. There is, therefore, no necessity for a data monitoring committee. Moreover, we do not expect any serious adverse events. Thus, no interim analysis is planned, and there are no stopping rules for safety issues. However, we plan to monitor the data quality in a blinded manner every 6 months during our regular study meetings. Data quality (e.g. proportion of missing values) and organisational or logistic issues will be reviewed and discussed in these meetings. In this way, any necessary actions to improve data quality and study logistics can be made early enough.

### Statistical analysis

The primary outcomes are the nursing home residents’ participation and activity, measured with the subscales of the ICF-based PaArticular Scales [17]. The evaluation of the impact of joint contractures and the effect of PECAN will be based on an intention-to-treat approach with a significance level of 0.05, which results in a Bonferroni-adjusted significance level of 0.025 for a single test. The analyses will use a generalised linear mixed-effect regression model to compare changes in the scale between the treatment groups over a year. Each nursing home will be given a random intercept. The analysis will be adjusted by the individual baseline values.

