### Participants and recruitment

#### Sample size calculation

The study uses a composite primary outcome with two components. To avoid a false positive outcome rate above 5% (significance level), we apply a Bonferroni correction on each of the two components and choose the component-wise significance level as 2.5% (0.05/2 = 0.025). Based on the data from a pilot study, we consider both components as distributional comparable, assuming that both have the same variability. Therefore, the sample size considerations for each component follow the same arguments. Thus, it is sufficient to compute an explicit sample size for one component.

Using the experience of the pilot study (publication in preparation), recruitment of 15 to 20 individuals per cluster is feasible. Thus, the sample size calculation assumed a fixed cluster size of 15 individuals and a free number of clusters. Using pilot data, the intraclass correlation coefficient was estimated at 0.38. This resulted in an inflation factor of (1 + (15 – 1) × 0.38) = 6.32. The subscale variance observed in the pilot study was about 200 (standard deviation 14.14); the effect difference for the participation subscale between the standard and intervention groups was assumed to be 10 at t_2_. The size of one group in this c-RCT is *n* = 241 (38 × 6.32) if the test is two-sided on a significance level of 2.5% and with a power of 80%. This results in a total of 16 clusters per study group (241 / 15 = 16.1). To compensate for individuals terminating the study early due to death or moving, 15% more individuals will be included in the study, resulting in 30 clusters with a cluster size of 18 individuals and two clusters with 19 individuals, the total study size being 578 individuals.

Current experience shows that a few clusters will possibly fail to recruit the necessary number of participants. In this case, we will recruit more participants in other clusters to compensate for this. To maintain the statistical power of the study, the following rule will be applied: number of participants to be additionally recruited in other clusters = 1.5 × number of participants that some clusters fail to recruit.

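### Testing both primary subscales at a fixed 0.025 gives up power on the second one; Holm's step-down keeps the same 5% family-wise limit at no cost in sample size

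*Protocol article*

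**What the plan says.** Two sections of the protocol article fix the same testing rule.

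- **Sample size calculation:** to hold the false positive rate at 5%, "we apply a Bonferroni correction on each of the two components and choose the component-wise significance level as 2.5" per cent. The size is worked out for one subscale, two-sided at 2.5% with 80% power, and taken to serve for the other as well.
- **Statistical analysis:** the primary evaluation follows "an intention-to-treat approach with a significance level of 0.05", "which results in a Bonferroni-adjusted significance level of 0.025 for a single test".

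The Primary outcome section explains why there are two tests. The pilot suggested that participation is hard to improve, the two constructs have no order of priority, and so "we decided that an improvement in any of the scales could be viewed as success".

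Neither section describes a step-down or any passing on of unused significance level. The rule is stated, not left open for a later analysis plan.

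**The concern.** Single-step Bonferroni judges each subscale at 0.025 whatever the other one shows. That is stricter than the stated 5% limit requires. If the first subscale is significant at 0.025, a family-wise error can arise only if that rejection was itself false or if the remaining hypothesis is true and rejected. Testing the remaining one at 0.05 keeps the total within 5% under any dependence between the two. This is Holm's procedure. It rejects everything Bonferroni rejects and sometimes more.

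Holm also suits the design. It needs no ordering of the hypotheses, which matches two unranked outcomes, whereas a fixed sequence would not.

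At stake is the claim on the second subscale. Both are primary outcomes, and the Discussion expects improvement in one or both. A second subscale with p between 0.025 and 0.05 would be reported as not shown, although the plan's own error limit does not demand that.

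**Working it through.** **Inputs from the sample size section.** Variance 200 (SD 14.14), difference 10 points at 12 months, two-sided level 0.025, power 80%, cluster size 15, intraclass correlation 0.38. Both subscales are assumed to be equally variable.

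**The plan's own figure.** With z(0.9875) = 2.241 and z(0.80) = 0.842, the sum is 3.083.

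- n per group before clustering = 2 × 200 × 3.083² / 10² = 38.02.
- Design effect = 1 + 14 × 0.38 = 6.32.
- 38.02 × 6.32 = 240.3, rounded up to 241. The stated 241 reproduces.

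The planned effect therefore gives each test statistic a mean (non-centrality) of 3.08 on a normal reference.

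**Assumptions added here.** The protocol gives no correlation between the two test statistics, so it was varied from 0 to 0.9. The 10-point effect is stated for participation. Applying it to activities follows the protocol's remark that the same reasoning serves both.

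**By hand at correlation 0.** Power at 0.025 is 0.800. Power at 0.05 is Φ(3.083 − 1.960) = 0.869. The chance of a p value between 0.025 and 0.05 is 0.069.

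- Both shown, Bonferroni: 0.800² = 0.640.
- Both shown, Holm (both p ≤ 0.05, at least one ≤ 0.025): 0.869² − 0.069² = 0.750.
- One given subscale, Holm: 0.800 + 0.069 × 0.800 = 0.855.
- At least one shown, either rule: 1 − 0.200² = 0.960.

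**Simulation over correlations** (4 million bivariate normal draws each, 10 points on both subscales):

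| Correlation | Both: Bonferroni | Both: Holm | Each: Bonferroni | Each: Holm | At least one: either rule |
|---|---|---|---|---|---|
| 0 | 64.1% | 75.1% | 80.0% | 85.6% | 96.0% |
| 0.3 | 66.6% | 76.6% | 80.0% | 85.0% | 93.4% |
| 0.5 | 68.7% | 77.9% | 80.0% | 84.6% | 91.3% |
| 0.7 | 71.3% | 79.4% | 80.0% | 84.1% | 88.7% |
| 0.9 | 75.0% | 81.5% | 80.0% | 83.3% | 85.0% |

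**Smaller effect on the second subscale** (10 points on the first):

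- *7 points* (non-centrality 0.7 × 3.083 = 2.16): Bonferroni power is about 46.6%. Power at 0.05 is Φ(2.16 − 1.96) = 0.579, so Holm at correlation 0 gives 0.80 × 0.579 + 0.20 × 0.466 = 55.6%. Simulation over correlations 0 to 0.7 gives 55.6–56.3%.
- *5 points:* second-subscale power rises from 24.2% to 31.9–33.8% over correlations 0 to 0.9.
- *No effect:* power on the subscale that responds barely moves (80.0% to about 80.2% at correlation 0).

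**Error control.**

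- No effect on either subscale: the family-wise error is identical under both rules, 4.95% at correlation 0 falling to 3.6% at 0.9.
- Effect on one subscale only: the false-claim rate on the other is 2.5% under Bonferroni. Under Holm at correlation 0 it is 0.025 + 0.025 × 0.80 = 4.5%, and it falls to about 3.8% at correlation 0.9. It stays within 5% throughout.

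**The case against.** The best defence is that nothing here is an error. Bonferroni is valid, prespecified, and used consistently in the sample size and analysis sections. More specifically:

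- **The success criterion gains nothing.** Holm makes its first rejection exactly when Bonferroni does, so the chance of at least one success is the same. This stands.
- **Power for both is not a stated target.** The protocol sets its 80% per subscale, where the gain is about 3 to 6 points, against about 6 to 11 points for showing both. This is fair, and both are given above.
- **The favourable case may not occur.** The protocol itself reports that participation was hard to improve in the pilot. If only one subscale responds, Holm adds almost nothing to power, and the false-claim rate on the other rises from 2.5% to as much as 4.5%. This is a real trade-off, but 4.5% is inside the limit the protocol chose.
- **Intervals.** Bonferroni has matching simultaneous 97.5% intervals. Under Holm, a second subscale with p between 0.025 and 0.05 would be declared significant while its 97.5% interval includes zero. This also stands, though the article commits to no such intervals for the primary outcomes.

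These points limit the benefit. None gives a reason, in terms of the stated 5% limit, to withhold the larger level from the second test.

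**Conclusion.** The concern holds as a matter of efficiency, not of validity. With unchanged numbers and the same 5% family-wise limit, Holm raises power per subscale from 80% to about 83–86%, and the chance of showing both by about 6 to 11 percentage points, across correlations 0 to 0.9. For a 7-point second effect, power on that subscale goes from about 47% to about 56%.

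These figures rest on a normal reference, the protocol's own variance and intraclass correlation, assumed correlations, and an effect on both subscales. The main success criterion and the sample size are unaffected. The change is worth making because it is nearly free, and because power is expensive in a trial of 32 homes with an intraclass correlation of 0.38.

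**What to change.** In the Statistical analysis section, replace the fixed 0.025 for each test with Holm's rule: compare the smaller of the two p values with 0.025; if it is significant, compare the larger with 0.05; otherwise declare neither. Record the change before any unblinded comparison.

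The sample size calculation can stay, since 80% at 2.5% becomes a lower bound on power per subscale. Report the 97.5% intervals alongside, and state in advance that they do not map exactly to the step-down decision for the second subscale.

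The cost is one sentence and no extra residents or homes. The price is the interval mismatch and a false-claim rate on a single unaffected subscale that may rise from 2.5% to about 4.5%, still within the 5% limit.

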#### Randomisation and allocation

Randomisation will be performed using stratified blocks. To ensure the intervention groups are balanced with respect to the location of the nursing homes, block randomisation will be performed taking two strata into account: (1) Halle (Saale) and (2) Rosenheim. Selection bias can be a problem in c-RCTs if participants are recruited after a cluster allocation has been implemented. Therefore, all clusters and participants will be recruited and assessed prior to randomisation. The clusters will be randomised by independent biostatisticians responsible for biometric supervision (UM and LL). Generating, operating and controlling the randomisation will follow the standard operating procedures of the biostatisticians’ institution and will be carried out by professionals who are not involved in trial activities at the nursing homes. Each of the nursing homes will be informed about its intervention allocation by fax by an independent data manager. Subsequently, the data manager will inform the study centres in Halle (Saale) and Rosenheim via fax about the allocation.

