#### Secondary analyses

The secondary outcome is the nursing home residents’ quality of life, which will be assessed at t_0_, t_1_ and t_2_ with the EQ-5D-5L [34, 35]. The analyses will also use a generalised linear mixed-effect regression model with EQ-5D-5L score changes over 1 year as the dependent variable, adjusted by the baseline value. Each nursing home will be given a random intercept.

The analyses of the primary and secondary outcomes will also allow for an additional adjustment for cluster and individual-specific confounding baseline variables such as age, gender, length of stay and grade of care at the individual level as well as ownership, number of residents, staff mix and ratio, and use of strategies for dealing with joint contractures or participation restrictions.

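### Homes are randomised within two regions but the stated models do not name region; if the regions differ in outcome, the test is conservative and forgoes precision

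*Protocol article*

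**What the plan says.** Under Randomisation and allocation, the protocol article says "block randomisation will be performed taking two strata into account: (1) Halle (Saale) and (2) Rosenheim". The stated aim is balance on location: "To ensure the intervention groups are balanced with respect to the location of the nursing homes".

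Under Statistical analysis, both PaArticular subscales are analysed with a mixed-effects regression comparing the arms, each at the Bonferroni-adjusted level of 0.025. On the terms of the model it says "Each nursing home will be given a random intercept. The analysis will be adjusted by the individual baseline values". Under Secondary analyses, the EQ-5D-5L model has the same structure: baseline value plus a random intercept per home.

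The same section adds: "The analyses of the primary and secondary outcomes will also allow for an additional adjustment for cluster and individual-specific confounding baseline variables". The cluster-level examples are "ownership, number of residents, staff mix and ratio, and use of strategies for dealing with joint contractures or participation restrictions". Region is not among them, although the list is worded as illustrative. The Additional measures section says that each home's location will be recorded.

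**The concern.** A factor that restricts the randomisation normally also belongs in the analysis. Balancing the arms within region takes any region difference out of the true sampling error of the arm contrast. A model without region still counts that difference as variation between homes, so the estimated standard error is larger than the true one. Confidence intervals are then too wide, the actual type I error lies below the nominal 2.5%, and the analysis does not collect the precision that the design provides.

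The matter deserves attention here because there are only 32 homes, the ICC is high at 0.38, and alpha is already halved. The strata also coincide with the two study centres, which run the facilitators' workshops, supply the mentors and organise data collection. Region could therefore carry differences in delivery and measurement as well as in geography.

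**Working it through.** **Inputs from Sample size calculation and Design (protocol article).** Variance 200 (SD 14.14), ICC 0.38, 15 residents per home, 16 homes per arm, difference 10 points, two-sided alpha 0.025 per subscale, power 80%, allocation 1:1.

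**Assumptions, because the documents give no figure.** The gap D in mean outcome between regions; 8 homes per arm in each region; equal cluster sizes; no baseline covariate, so D stands for the gap that would remain after adjustment.

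**1. The plan's own figure.** The unrounded n per arm before clustering is 2 × [14.14 × (2.241 + 0.842) / 10]² = 38.0. The design effect is 1 + 14 × 0.38 = 6.32. Then 38 × 6.32 = 240.2, stated as 241, and 241 / 15 = 16.1, taken as 16 homes per arm. The plan's figure reproduces.

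**2. Precision of a home mean.** Variance = 200 × (0.38 + 0.62/15) = 76 + 8.27 = 84.27. The standard error of the arm contrast is √(2 × 84.27 / 16) = 3.25. Power is 79.9% by the normal approximation and 76.1% with a t reference on 30 df. The sample size takes no credit for stratification.

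**3. Effect of a region gap.** With two equal regions, the gap contributes D²/4 to the variance between homes. If the pilot ICC already contains it, the within-region variance of a home mean is v = 84.27 − D²/4, and the true standard error is √(2v/16). A model without region has an expected residual variance of v + 8D²/30, because each of 32 homes lies D/2 from the overall mean: 32 × D²/4 = 8D², spread over 30 df. The ratio of estimated to true standard error is about √[(v + 8D²/30) / v].

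- D = 2.5: v = 82.70, estimated 84.37, ratio 1.010
- D = 5: v = 78.02, estimated 84.68, ratio 1.042
- D = 8: v = 68.27, estimated 85.33, ratio 1.118

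**4. Test size and power.** These come from simulations of 32 home means, 100,000 runs per scenario, with t-tests at 0.025 with and without region:

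| Gap D | Actual alpha without region | Power without region | Power with region | Forgone |
|---|---|---|---|---|
| 0 | 0.026 | 76.3% | 76.2% | none |
| 2.5 | 0.024 | 76.4% | 77.0% | 0.6 points |
| 5 | 0.021 | 76.8% | 79.5% | 2.7 points |
| 8 | 0.013 | 77.8% | 84.9% | 7.1 points |

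With region in the model, simulated alpha is 0.026 at every gap, which is nominal within simulation error. At D = 0 the extra term costs 0.1 to 0.2 points of power.

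**5. The other reading of the ICC.** If region variance comes on top of the pilot variance, power with region stays at 76.2% whatever the gap. Without region it is 75.6% at D = 2.5, 73.5% at D = 5 (alpha 0.021) and 70.6% at D = 7.07 (alpha 0.017).

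**The case against.** The strongest defence is that a journal article condenses the plan and that a statistical analysis plan not shown here may include region. The article does not say that its covariate set is complete, its list of further covariates is open, and home location is recorded. All this stands as a reason for caution. It does not dispose of the point. The article states the terms of the primary model, and the open list concerns optional adjustment described under secondary analyses, which does not put the stratification factor into the primary test.

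The second defence concerns size, and it stands. The effect needs a gap that remains after adjustment for each resident's baseline value. A stable difference in level between regions would be at least partly absorbed by that adjustment. The calculation has no baseline covariate, and the number of homes per region is not given. A gap of 8 points would be 80% of the difference that the trial calls clinically meaningful, so the upper end of the range should not be read as expected.

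A reader might infer more than the documents support:

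- That the test is conservative and the intervals wrong as a matter of fact. This holds only if the regions differ, and no figure is given for that.
- That power falls below plan. If the ICC already contains region variance, power without region does not drop as the gap grows (76.3% at 0, 77.8% at 8 points), so what is missed is a possible gain. Only under the other reading, in which region variance is additional, does power fall.
- That the economic bootstrap must also be resampled within region. The article leaves the resampling scheme open, and nothing in this check bears on it.

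**Conclusion.** The mismatch is real: region governs the randomisation, and neither the stated primary model nor the stated EQ-5D-5L model names it. The consequence is conditional. With a residual region gap, the standard error is too large, the test is conservative and available precision goes unused; without one, nothing is lost. Validity is not threatened, because the error is on the conservative side.

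Over assumed gaps of 0 to 8 points, with an even split of homes, no baseline covariate and region variance inside the ICC, the power forgone runs from none to about 7 points against a region-adjusted model. The change is worth making because the possible gain clearly exceeds the cost, and not because a loss has been shown.

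**What to change.** Name region (two levels, as used in the randomisation) as a fixed effect in the primary models for both PaArticular subscales and in the EQ-5D-5L model, before the outcome data are unblinded. If the statistical analysis plan already does this, a sentence confirming it is enough. The stratum of each home is known from the randomisation, so no new data are needed. The cost is one of about 30 degrees of freedom, or about 0.1 to 0.2 points of power if the regions do not differ.
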